### Inclusion criteria

Participants must meet all of the following criteria to be enrolled in this study:

#### Cases

Men aged 21–49 years.Men with a female partner aged 21–39 years.Couples who are not able to conceive for at least 12 months of regular, unprotected intercourse.Couples who are Singapore citizens or permanent residents.

#### Controls

Men aged 21–49 years.Men with a female partner aged 21–39 years.Men with proven fertility indicated by female partners who are currently pregnant and with viable intrauterine pregnancy at gestational weeks of less than or equal to 16 at the time of the study.Couples with attempted time to conceive within 12 months to achieve this pregnancy.Couples who are Singapore citizens or permanent residents.

### Exclusion criteria

Participants meeting any of the following criteria will be excluded from this study:

#### Cases

Male infertility of a known aetiology, including azoospermia, retrograde ejaculation, genetic disorders, cancer treatment, or testicular trauma.Female infertility diagnosis as confirmed by diagnostic imaging or having severe endometriosis.Female partners with an irregular menstrual cycle of >35 days.Couples with known chromosomal abnormalities.

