#### Controls

Couples who achieve pregnancy after oocyte or spermatozoa donation.Couples with known chromosomal abnormalities.Female partners with known uterine abnormalities.

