Given that the fertility index comprises male and female factors, we will perform additional analyses to evaluate the individual performance of the index that includes only male factors or female factors using the AUROC. We will also evaluate the performance of the male factor index, with adjustment of female factor index.

#### Aim 3

We will use multivariable linear regression to examine the association between modifiable factors and semen parameters, adjusting for sociodemographic factors.

To understand the relationships between male factors and fertility indices across different conception methods, we will replicate the above analyses by examining outcomes based on assisted and unassisted conception. To assess potential selection bias in both studies, we will compare baseline characteristics between participants with and without a complete set of data. We will use multiple imputation by chained equation to handle missing values.^54^ Sensitivity analyses will be conducted using only samples with complete data. To further ensure robustness, we will test interactions between male and female factors and stratify analyses by key confounders. Statistical analyses will be conducted using the Stata Statistical Software.

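### Long cycles and severe endometriosis are excluded from cases but not from controls, which biases the female-factor coefficients, chiefly BMI, in the Aim 2 fertility index

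*Protocol article*

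**What the plan says.** The protocol article lists exclusions separately for the two groups.

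- Cases only: "Male infertility of a known aetiology, including azoospermia, retrograde ejaculation, genetic disorders, cancer treatment, or testicular trauma"; "Female infertility diagnosis as confirmed by diagnostic imaging or having severe endometriosis"; and "Female partners with an irregular menstrual cycle of >35 days".
- Controls only: "Couples who achieve pregnancy after oocyte or spermatozoa donation" and "Female partners with known uterine abnormalities".
- Both groups: "Couples with known chromosomal abnormalities".

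The inclusion criteria do not restore symmetry. Age and residency limits match, and controls must satisfy "Couples with attempted time to conceive within 12 months to achieve this pregnancy", but nothing limits their cycle length, endometriosis or male history. Assisted conceptions can be controls, because the Statistical analysis plan section says that "we will replicate the above analyses by examining outcomes based on assisted and unassisted conception".

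For Aim 1, the plan adjusts for female factors related to both male factors and pregnancy, and will explore propensity weighting. For Aim 2, it names female age, BMI, smoking, diet, alcohol and folic acid among the predictors, and weights the model to the population prevalence of pregnancy within a year. Neither aim names cycle length or endometriosis. The selection-bias check compares participants with and without complete data. The limitations in the Discussion cover recall, residual confounding and generalisability, but not unequal eligibility.

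**The concern.** A case-control contrast is interpretable when both groups are drawn from the same restricted population of couples. Here a condition that impairs conception is removed from the non-conceiving group and left in the conceiving group. Whatever travels with that condition then differs between groups because of eligibility, even if it has no effect on fertility.

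The clearest instance is the cycle criterion. If women with long cycles are heavier on average, heavier women are taken out of the cases and kept among the controls. Female BMI then looks less harmful than it is, or even favourable. BMI is a named predictor in the index, and its coefficient becomes integer points intended for community use. The issue may matter more in this study because both groups are also recruited through HELMS, a programme for women with obesity.

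**Working it through.** **1. The two lists side by side (Exclusion criteria)**

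| Condition | Cases | Controls |
|---|---|---|
| Female cycle >35 days | excluded | not restricted |
| Severe endometriosis | excluded | not restricted |
| Imaging-confirmed female infertility diagnosis | excluded | not restricted |
| Male infertility of known cause | excluded | not restricted |
| Known uterine abnormality | not named | excluded |
| Gamete donation | not applicable | excluded |
| Known chromosomal abnormality | excluded | excluded |

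Only one condition is treated alike by name.

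**2. The plan's own figure (Sample size)**

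Inputs: male BMI difference 1.3, SD 4, two-sided 5%, power 90%. n per group = 2 × (1.960 + 1.282)² × 4² / 1.3² = 199 by the normal approximation, or 200 with the t distribution. 200 × 1.2 = 240 per group, 480 in total. This reproduces the plan and does not depend on the exclusions.

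**3. Illustration of the crude distortion**

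The document gives no prevalences, so all inputs here are assumptions. Let a share q of otherwise eligible women in each group have cycles >35 days, with mean BMI d units higher. Removing them from cases only makes control women heavier by q × d:

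- q = 5%, d = 2: 0.05 × 2 = 0.1 kg/m2
- q = 20%, d = 4: 0.20 × 4 = 0.8 kg/m2

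Now take a binary exposure with no true effect, present in 30% of women with regular cycles and 50% to 60% of those with long cycles. Exposure prevalence among cases is 0.30.

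- q = 5%, 50%: controls 0.05 × 0.5 + 0.95 × 0.3 = 0.31; OR = (0.30/0.70)/(0.31/0.69) = 0.95
- q = 20%, 60%: controls 0.20 × 0.6 + 0.80 × 0.3 = 0.36; OR = (0.30/0.70)/(0.36/0.64) = 0.76

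**4. What reaches the male estimate**

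With an assumed spousal BMI slope of 0.2 to 0.4, the crude male BMI contrast moves by 0.2 × 0.1 = 0.02 to 0.4 × 0.8 = 0.32 kg/m2, that is 1.5% to 25% of 1.3, against the hypothesised direction. Power at 200 per group would be 89% to 69%. This is the crude contrast, not the adjusted model that the plan specifies.

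**5. What the adjusted model does**

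A simulation assumed 10% long cycles, +4 kg/m2 female BMI, spousal slope 0.3, and a true log odds ratio of 0.05 per unit for both male and female BMI, with long-cycle cases removed.

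| Model | Male BMI | Female BMI |
|---|---|---|
| Adjusted for female BMI, not cycle status | 0.050 | 0.031 |
| Adjusted for cycle status as well | 0.049 | 0.050 |

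Without cycle status, the female coefficient is 0.031/0.05 = 62% of its true value, while the male coefficient is intact. A repeat with a female BMI SD of 4 within cycle groups gave the same pattern, with somewhat stronger attenuation of the female coefficient. The pattern is what matters; the amount depends on the inputs.

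**The case against.** The strongest reply is that analysis can repair this. That is right for the correlates. If cycle status is in the model, the long-cycle stratum contains only controls and is perfectly predicted, so the other coefficients come from the regular-cycle couples, exactly as under restriction. Only the coefficient of the condition itself is lost. A reader might infer from the missing overlap that no adjustment can help, but that does not follow. What stands against the plan is that it does not name cycle status or endometriosis as adjusters. Weighting to the population prevalence corrects the ratio of cases to controls, but cannot restore kinds of couples that were never enrolled as cases.

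A reader might also infer that the male BMI effect in Aim 1 is seriously distorted, for instance by setting a female BMI shift against the 1.3 kg/m2 in the sample size section. The document does not support this. The 1.3 is a male BMI difference, and the spousal route to the male estimate largely closes once female BMI is adjusted for.

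Some asymmetries are weaker than they look. Known male cause and a female infertility diagnosis help to define a case, and will be uncommon in couples who conceived within 12 months, though assisted conception keeps them possible. Conception within 12 months also depletes long cycles among controls, so the upper part of the assumed range may be too high. The imaging criterion for cases may cover much of the uterine item. The donation exclusion follows from controls being pregnant. None of this removes the asymmetry in cycle length and severe endometriosis.

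An intention to isolate unexplained or male-factor infertility is legitimate, but it argues for the same restriction in controls.

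**Conclusion.** The concern holds in a limited form. Cycles >35 days and severe endometriosis are covariate restrictions placed on one outcome group, and nothing planned restores balance. The main consequence is bias in the female coefficients of the Aim 2 index. For BMI it runs towards the null or a favourable direction, on the assumption that long cycles go with higher BMI. Aim 1 male estimates are affected mainly where a male factor is related to an excluded condition beyond the adjusted female factors. The size cannot be derived from the document; the figures in the working show the range under stated assumptions and are not estimates. The planned sample size is not in question here.

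**What to change.** Apply one set of history-based exclusions to both groups: cycle >35 days (before this pregnancy, for controls), known severe endometriosis, known male aetiology and known uterine abnormality, alongside the chromosomal criterion already shared. Table 1 lists only broad medical and reproductive history for both partners, so add these items explicitly to the collection forms.

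Make couples who meet the common list the primary analysis set for Aims 1 and 2, with all enrolled couples as a sensitivity analysis. This also handles couples already enrolled. State as a limitation that imaging-confirmed diagnoses are ascertained unequally, because many pregnant controls will have had no work-up; a common list cannot cure that item.

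The cost is a minor amendment and some loss of controls from the primary analysis, or their replacement while recruitment continues. At an assumed 5% with long cycles the loss is 0.05 × 240 = 12 controls. At 20%, probably too high for women who conceived within 12 months, it is 48. A few cases with known uterine abnormality would also be lost. The target of 480 couples stays as it is.

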#### Controls

Couples who achieve pregnancy after oocyte or spermatozoa donation.Couples with known chromosomal abnormalities.Female partners with known uterine abnormalities.

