## Introduction

 Singapore has been grappling with a persistently low total fertility rate of 1.1 since 2018, which dropped below 1.0 in 2023.^1^ Despite the implementation of comprehensive pronatalist policies, this rate remains among the lowest globally, much like many developed countries in the region.^2 3^ Based on the WHO global report, approximately 1-in-6 couples experience challenges in achieving pregnancy.^4^ Subfertility is defined as the failure to achieve conception after 12 months of regular, unprotected sexual intercourse.^5 6^ Given the high prevalence of poor fertility globally, it is crucial to thoroughly examine the factors that impact reproductive health. Historically, fertility research has been primarily focused on women,^7^ but preliminary estimates suggest that males are solely responsible for 20–30% of cases and contribute to 50% overall.^8^ However, our understanding of the causes, impact and consequences of male reproductive health remains inadequate. Emerging reports indicate that men with impaired fertility bear a higher disease burden, with an increased risk of incident diseases such as heart disease and cancer, as well as premature mortality compared with men with normal fertility.^9^ Following the Paternal Origins of Health and Disease (POHaD) concept, as an extension of the Developmental Origin of Health and Disease paradigm, there is increasing evidence suggesting that the father’s health may significantly affect sperm quality and the health of the offspring.^10^,^12^ Consequently, gaining an understanding of the role of male factors in reproductive health is vital for developing effective interventions to address the fertility crisis, informing strategies for male health promotion and management, and potentially leading to improved health of future offspring.

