## Methods and analysis

### Study design and setting

This is an unmatched case-control study involving 240 couples with impaired male fertility (cases) and 240 couples with normal male fertility (controls). Participants are planned to be recruited between July 2024 and June 2026 from KK Women’s and Children’s Hospital (KKH), Singapore. The current protocol is version 1, dated 26 March 2024.

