### Sample size

There is no straightforward, universally accepted method to estimate the required number of participants for developing a multivariable prediction model. Thus, we employed a few alternative methods to estimate the sample size required. We used paternal BMI as an indicator reflective of paternal lifestyle and metabolic factors that are associated with successful pregnancy and expect that it may be retained in the prediction model. Based on the assumption that males with impaired fertility will have an average BMI 1.3 unit higher than the fertile males,^55 56^ and considering a BMI SD of 4 kg/m^2^, a two-sided 5% type 1 error rate and a power of 90%, the minimum required sample size to detect a difference in BMI between cases and controls is 400 couples (200 cases:200 controls). Considering a variance inflation factor of 1.2 for adjustment of maternal factors and other covariates, the study will need to recruit 480 couples (240 cases:240 controls).

Previous studies have reported the use of the event per variable (EPV) ratio:the number of events (success pregnancy) divided by the number of regression coefficients in the model to determine the sample size of a multivariable model.^57^ An EPV of at least 10 has been recommended to avoid overfitting.^58^ We estimate 15 regression coefficients based on the independent male predicting factors of successful pregnancy in the logistic model. Following this guideline, we require 150 events. Given the observed pregnancy rate of 48% in the population,^59^ the total sample size calculated to achieve this number of events is approximately 313 (150/0.48). By accounting for a variance inflation rate of 1.2 for correlation between male and female factors, we will require 376 couples (188 cases:188 controls) in the study.

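### Own-gamete assisted pregnancies count as proof of normal male fertility, so the main Aim 1 and Aim 2 comparisons may contain misclassified controls

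*Protocol article*

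**What the plan says.** All references are to the protocol article.

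- **Inclusion criteria, Controls.** The man's fertility is established by his partner's pregnancy: "Men with proven fertility indicated by female partners who are currently pregnant", viable, intrauterine and at no more than 16 weeks. A second criterion limits the time taken: "Couples with attempted time to conceive within 12 months to achieve this pregnancy". Neither mentions how conception occurred.
- **Exclusion criteria, Controls.** The only exclusion that concerns mode of conception is "Couples who achieve pregnancy after oocyte or spermatozoa donation". The others are known chromosomal abnormalities and known uterine abnormalities.
- **Exclusion criteria, Cases.** Cases are excluded for "Male infertility of a known aetiology, including azoospermia, retrograde ejaculation, genetic disorders, cancer treatment, or testicular trauma". The control list has no counterpart.
- **Introduction.** Subfertility is "failure to achieve conception after 12 months of regular, unprotected sexual intercourse". The inclusion criteria for cases apply the same standard.
- **Statistical analysis plan, text under Aim 3.** To look across conception methods, "we will replicate the above analyses by examining outcomes based on assisted and unassisted conception".

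**The concern.** The two groups are not defined by the same standard. A couple becomes a case by failing to conceive through intercourse. A couple becomes a control by being pregnant, by any route except donor gametes. A pregnancy after assisted conception with the man's own sperm does not show that he would have conceived by intercourse, so for that man the control label is unproven.

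The one-sided exclusion sharpens this. A man who could not enter as a case because of a known male cause could enter as a control if treatment with his own sperm succeeded within the time limit.

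The planned repeat by mode of conception indicates that the investigators expect such couples. Cases have no qualifying pregnancy and there is a single visit, so assisted conceptions in the index pregnancy can come only from the control side.

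Three results are exposed: the Aim 1 logistic and LASSO analyses; the Aim 2 index, which takes its male factors from Aim 1; and the comparisons of sperm RNA and methylation between cases and controls. A factor weakened in the LASSO step may be dropped before the index is built, and a later stratified repeat does not restore it to the main index.

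**Working it through.** **1. The plan's own figure.** The Sample size section assumes that "males with impaired fertility will have an average BMI 1.3 unit higher than the fertile males", with SD 4 kg/m², two-sided alpha 5% and 90% power.

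- n per group = 2 × 4² × (1.960 + 1.282)² / 1.3² ≈ 199, against the stated 200.
- 400 × 1.2 (the stated variance inflation factor) = 480, as stated.
- Standard error of the adjusted difference with 240 per group = 4 × √[1.2 × (1/240 + 1/240)] = 0.40.
- Power = Φ(1.3/0.40 − 1.96) = Φ(1.29) = 90.1%.

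The stated sample size reproduces, and no stated figure is in dispute.

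**2. Dilution if assisted men are kept.** The share *a* of controls who conceived with assistance is not in the document, so 5, 10 and 20% are assumptions. As an unfavourable case, suppose that all these men have the case-group mean BMI. The expected difference is then 1.3 × (1 − a), and power = Φ(1.3(1 − a)/0.40 − 1.96).

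**3. Removal.** If they are set aside, the control group is 240 × (1 − a), the difference stays at 1.3, and the standard error is 4 × √[1.2 × (1/240 + 1/n₀)].

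| Assumed share | Difference if kept | Power if kept | Controls left if removed (n₀) | Power if removed |
|---|---|---|---|---|
| 5% | 1.24 | 87.0% | 228 | 89.4% |
| 10% | 1.17 | 83.3% | 216 | 88.6% |
| 20% | 1.04 | 73.9% | 192 | 86.5% |

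**4. A milder assumption.** If only half of the assisted men resemble cases, the difference is 1.3 × (1 − a/2). Keeping them gives 88.7% power at a 5% share and 87.0% at 10%, against 89.4% and 88.6% after removal. The gain from removal is then 0.7 and 1.6 points.

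**5. If all assisted men are in truth fertile.** Keeping them retains 90.1%. Removing them costs 0.7, 1.6 or 3.6 points at shares of 5, 10 or 20%.

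**6. Odds-ratio scale, as illustration.** Assume that 30% of truly fertile men are exposed and the true odds ratio is 2.0, so 46.2% of cases are exposed. If assisted men carry the case exposure rate, exposure among controls rises to 30.8, 31.6 or 33.2% at shares of 5, 10 or 20%. The expected odds ratio falls to 1.93, 1.85 or 1.72.

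**The case against.** The case on the other side is substantial.

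- **The plan already has an unassisted comparison.** The repeat by conception mode provides it, so the dispute is partly about which analysis is primary. This stands, and it is why the remedy is small. It does not change what the main Aim 1 and Aim 2 models contain as described.
- **The 12-month limit removes many treated couples.** It should. On a plain reading it covers the whole attempt, although the article does not say how time under treatment counts. Couples who went to treatment early for a known problem still pass. By the article's own definition, a couple pregnant before 12 months has not been shown to be subfertile. Their unaided fertility is unknown, and a reader should not infer that every assisted control is a misplaced case.
- **Treatment may be for a female reason.** The exclusions for irregular cycles and female infertility diagnosis apply to cases only, so fertile men with treated partners can be controls. This stands, and it makes the power figures for case-like men an upper bound on the loss for each share.
- **Aims 1 and 2 speak of pregnancy as the outcome.** An assisted pregnancy satisfies that wording. It does not satisfy the label of normal male fertility or the claim of proven fertility, and those define the reference group.
- **Direction is not guaranteed.** Lifestyle exposures refer to the past month. Couples who have been through treatment may have changed smoking, diet or supplements, which could widen some contrasts.
- **An eligibility bar would have a cost.** It would stop recruitment of the couples that the repeat by conception mode needs. This also stands.

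**Conclusion.** The concern holds in a limited form. As written, the eligibility rules let own-gamete assisted pregnancies stand as proof of normal male fertility, and the main Aim 1 and Aim 2 analyses and the case-control molecular comparisons may therefore include misclassified controls. The 12-month limit and the planned repeat reduce this without removing it.

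The size cannot be taken from the document. For paternal BMI, power would fall from 90% to about 87, 83 or 74% at assumed shares of 5, 10 or 20%, provided that every assisted man resembles the cases. The loss is smaller if some were treated for female reasons. For other exposures a bias towards no effect is likely but not certain.

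A reader might infer that every male-factor contrast in the study is diluted. The document does not support that. The Aim 3 regressions of semen parameters on exposures are not case-control contrasts, and the unassisted part of the planned repeat is free of this misclassification.

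**What to change.** 1. Define controls who conceived without assisted reproduction as the primary control set for Aims 1 and 2, including the LASSO selection that feeds the index.
2. Report the analysis that includes assisted-conception controls as the sensitivity or stratified analysis already foreseen under Aim 3. No eligibility bar is needed, and these couples can still be recruited.
3. Reconcile the known-male-infertility exclusion between cases and controls, or give the reason for the difference.

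The cost is one analysis-set definition and some controls outside the primary analysis. If those men are in truth fertile, the power lost is about 1 point at a 5% share and about 4 points at 20%. If they all resemble cases, the restricted set has the higher power at each assumed share: 89.4 against 87.0%, 88.6 against 83.3%, and 86.5 against 73.9%.
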